**Fig. 3 Fig3:**
[figure not shown]
Initial program theory of the preventive integrated eHealth (PIE) approach

#### Study population

Adults (≥ 18 years) with low SEP living in the Netherlands are eligible for participation. Low SEP is defined by educational level, income or area of residence. For education, low SEP is based on the highest level of education obtained with a degree and defined as level 0–2 of the International Standard Classification of Education (ISCED) [46]. ISCED 0–2 includes people with elementary school or less, vocational practical education, lower secondary school, first classes of higher secondary education and lower vocational school [47]. For income, low SEP is defined as an income level not exceeding 120% of the social minimum income as noted by the Dutch government. For neighborhoods, low SEP is defined as neighborhoods that have a SES-WOA-score lower than 0,1. The SES-WOA-score is an aggregate socioeconomic status score based on the financial prosperity, educational level and work participation of households in this neighborhood. This score is calculated by the Statistics Netherlands for all of the Dutch municipalities [48].

Potential participants will be excluded if they are not of sufficient competence (i.e. do not have control over their own financial or care choices) or have mild cognitive impairment.

In addition to participants of the intervention, we invite care professionals and stakeholders who are part of the planning, implementation and organization of the PIE-approach to participate in the evaluation by means of semi-structured in-depths interviews.

#### Recruitment procedure PIE-study

All persons participating in the preventive integrated eHealth approach will be invited to participate in the PIE-study personally, either by the care professionals or the researchers. Potential participants receive an invitation letter with a link to a video explaining the study details and have the opportunity to ask the researchers questions about the study through email, telephone or in person, depending on way the intervention is offered locally. The control group will be recruited from neighborhoods with a similar socioeconomic profile according to their SES-WOA-score but which do not participate in offering the preventive integrated eHealth approach, through recruitment strategies specifically aimed at persons with low SEP. Eligible care professionals will be personally invited by the researcher to participate in an interview. Written or digital informed consent will be obtained from all participants prior to participating.

#### Data collection process

This mixed methods study makes use of quantitative methods in the form of digital or paper surveys for the participants at 0, 3 and 12 months after participants joined the PIE-approach. Qualitative methods include the use of four data sources: open questions in surveys and focus groups for participants, interviews with professionals, and ethnographic observation on location of pilots, including the scrutiny of policy and evaluation documents. The evaluation plan is presented in Table 3.

**Table 3 Tab3:** Preventive integrated eHealth approach evaluation plan

Research question	Data collection	Data source
1. How were the different steps of the PIE-approach carried out for each location?	¬ Detailed description of resources used ¬ Data on reach, dose of intervention delivered and received	• Policy and evaluation documents • Ethnographic observation and logbook • Interviews with professionals
2. Who took part in the PIE-approach?	¬ Demographics: age, sex, migration background, educational level, occupational status, household income and composition, area of residence, digital literacy, health literacy, financial strain	• Participant questionnaire 0 months
3. What different strategies for active and personal invitation and recruitment were used and how do they stimulate participation?	¬ Detailed description of resources used ¬ Detailed description of responses to resources used and triggered mechanisms that lead to participation	• Policy and evaluation documents • Ethnographic observation and logbook • Interviews with professionals • Focus groups with participants
4. What effect did the use of an eHealth tool elicit among the participants and why?	¬ Detailed description of responses to resources used and triggered mechanisms regarding use of the eHealth tool	• Interviews with professionals • Focus groups with participants
5. What effect did the personal consultation with a care professional elicit among the participants and why?	¬ Detailed description of responses to resources used and triggered mechanisms regarding the personal consultation	• Interviews with professionals • Focus groups with participants
6. What actions did the participants take after the PIE-approach and why?	¬ Data on goals set and taken actions after the PIE-approach ¬ Detailed description of responses to resources used and triggered mechanisms that lead to goals set and taken actions	• Participant questionnaire 3, 12 months • Policy and evaluation documents • Interviews with professionals • Focus groups with participants
7. What kind of barriers and facilitators did participants and professionals experience for each step of the PIE-approach and what mechanisms were triggered?	¬ Data on appreciation of the steps of the PIE-approach ¬ Detailed description of responses to resources used and triggered mechanisms regarding positive and negative aspects	• Participant questionnaire 3, 12 months • Interviews with professionals • Focus groups with participants
8. What was the outcome of the PIE-approach on self-assessed overall health and well-being, health behaviors, underlying determinants and the intention to change?	¬ 17 items Positive Health measuring scale ¬ General self-assessed health, fruit and vegetable intake, weekly physical activity, duration of sleep, alcohol consumption, smoking habits, financial strain, stress inducing life events and perceived stress, intention to change health behavior, self-reported BMI	• Participant questionnaire 0, 3 and 12 months • Control group questionnaire 0, 3 and 12 months

#### Quantitative data collection

Participants will fill in a paper or digital survey at three moments (see Table 3). At T = 1 (0 months) the survey will include sociodemographic features, health and digital literacy, perceived stress including financial stress, self-assessed health and general well-being, and health related behaviors such as physical activity, vegetable and fruit intake, alcohol use, smoking and sleep. At T = 2 (3 months) and T = 3 (12 months) questions relating to stress, self-assessed health, and health behaviors will be repeated, with additional questions related to the process evaluation indicating participants’ experience with and appreciation of each element of the PIE-approach. The control group receive the survey at the same time points, including the same questions with exception of the questions relating specifically to the experience of the different steps of the PIE-approach.

As our primary outcome, the 17 items Positive Health measurement scale will be used, which is a 17-item measurement model based on the 44-items MPH dialogue tool. It has been developed to measure the effects of interventions on a broad perspective of health dimensions and uses a six factor structure, comprising the factors physical fitness, mental functions, future perspectives, contentment, social relations, and daily life-management (slightly different from the dimensions used in the dialogue tool) to provide a broad understanding of self-assessed health-related quality of life. An average score (1–10) for each factor is calculated. Higher scores are associated with better quality of life. The 17-items Positive Health measurement scale is in Dutch, developed by Dutch researchers and validated for use in the Netherlands [49] and derived from the concept of Positive Health. Positive Health is a concept of health proposed by Huber that describes health ‘as the ability to adapt and self-manage, in the face of physical, mental, and social challenges’ [40]. This allows to take a broader look at one’s perceived health than just as a ‘state of complete physical, mental and social well-being’ according to the World Health Organization [50]. In addition to this, the 1-item self-assessed general health (5 point Likert scale; very well-well-not well, not poor-poor-very poor) is used as an overall widely used indicator of health status [51].

Secondary outcomes will include questions on the experience of stress (adverse life events, financial stress (Psychological Inventory of Financial Scarcity [52], stress at home, work, or otherwise, and the handling of stress) and lifestyle behaviors (intake of fruit and vegetables, weekly exercise, hours of sleep, alcohol intake and smoking habits).

Questions on sociodemographic characteristics will include gender, age, level of education, income, employment status, country of birth for the participant and their parents, marital status, and household composition. Additional factors such as health literacy (Set of Brief Screening Questions [53] and digital skills (adapted version of the Digital Difficulties Scale [54]) will also be evaluated.

#### Qualitative data collection

Participants will be invited for a focus group discussion half a year after inclusion of a minimum of 20 participants, or when inclusion has ended (see Table 3). During the focus groups, the different program theories will be tested and refined according to realist interviewing principles [55, 56]. The main question concerns what generative causal mechanisms were triggered by the PIE-approach. The IPT for the four steps of the PIE-approach will be discussed in depth, how each step affected the participant and what contextual factors, facilitators, and barriers played a role in their experience and what mechanisms it triggered. The use of focus groups allows for the exploration of a plethora of different mechanisms and how participants view these in relation to others [57].

Semi structured in-depth interviews will be held with care professionals approximately 3 months after inclusion of 20 participants, or when inclusion has ended, to ensure that the professionals have enough time to gain valuable experience with the PIE-approach (see Table 3). In these realist interviews, the IPT will be tested and refined from the perspective of the care professional. In addition, reach, dose of the intervention delivered by care professionals, dose of the intervention received by participants, facilitators and barriers of the PIE-approach, and contextual factors that have influence on user engagement will be addressed.

For each pilot, on location field observations will be carried out on the content of care delivery, interactions between care professionals and participants, together with participants’ responses to the PIE-approach (see Table 3). Field notes together with policy and evaluation documents will inform the testing and refining of the IPT.

### Phase 4 Data analysis

### Quantitative analysis

For statistical analysis, the propensity score matching technique will be used as an alternative design to evaluate the effectiveness of the PIE-approach since a randomized controlled trial is not feasible or desired in this situation [58, 59]. Allocation of persons to the intervention and control group is not random, so differences between the intervention and control group may exist. The goal of the propensity score method is to balance two non-equivalent groups on observed covariates to get more accurate estimates of the effect of the PIE-approach. The propensity score is the probability of being exposed to the PIE-approach given the observed characteristics of a person [60, 61]. Propensity scores will be estimated for all individuals by regressing the participation status in the PIE-approach (yes/no) on the measured baseline characteristics using a logistic regression model.

Preferably, individuals participating in the PIE-approach and controls will be matched based on their propensity score (propensity score matching). Then, the intervention effects will be estimated comparing the primary, and secondary, outcomes between the participating and not-participating individuals in the matched sample. If the number of matched partners is less than anticipated, other propensity score methods (e.g. inverse probability of treatment weighting or regression adjustment) will be considered. We will use multiple regression models for the quantitative data using the matched data. Descriptive statistics will be used to describe the sociodemographic characteristics of the study sample and implementation results (such as reach, dose delivered and received).

Under the assumption of a power of 80% and a significance level of 5% (two sided), and a (norm-based) standard deviation of 1.79, we would be able to detect a difference of approximately 0.55 point in the score of one of the six domains of the 17 items MPH measuring scale with 175 participants with completed questionnaires and participating in the PIE approach. Due to possible mismatches between the propensity scores of the intervention and the control group, we aim for a sample of 200 respondents in both groups. Based on this calculation, we aim to recruit between 20 and 40 participants from each location for a maximum of 10 pilot locations.

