### Phase 3 Data collection

#### Study design and setting

The PIE study applies a quasi-experimental, non-randomized controlled trial design, with a follow-up period of 12 months within the realist evaluation. An intervention group of participants in the PIE-approach will be compared to a control group consisting of Dutch citizens who do not participate in the PIE-approach. The study will make use of natural field experiments (‘pilot locations’) in a maximum of 10 locations in the social or primary healthcare domain across the Netherlands. The pilot location will be similar in offering the four steps of the PIE-approach. However, they will differ in their local context, the way people are directed towards the eHealth tool, the specific support and guidance of participants and their aftercare, in line with local preferences and possibilities.

Recruitment of the pilot locations is facilitated through the network of VitaValley, an organization that focuses on innovation in preventative healthcare. Health disparities are becoming an increasing focus of Dutch government and municipality policies [44], which creates interest and funding to create experience with new tactics such as the PIE-approach. Social welfare and healthcare professionals who work with low SEP groups, and experience their daily struggles, have asked for national attention and sterner policies [45] to decrease health inequality. Together with the increased attention for preventive health strategies for non-communicable diseases, it is a topic that is of interest to many to ensure that scarce time, effort, and resources are directed towards effective care.

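### The stated 80% power for a 0.55-point difference assumes independent participants, although the intervention group is nested in at most 10 deliberately different locations; the named regression should account for location

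*Protocol article*

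**What the plan says.** The power statement in the Quantitative analysis section uses individual-level inputs only: 80% power, two-sided 5% significance, a "norm-based) standard deviation of 1.79", and the conclusion that "we would be able to detect a difference of approximately 0.55 point in the score of one of the six domains" of the primary scale "with 175 participants with completed questionnaires and participating in the PIE approach". The target is then raised to 200 per group. The only reason given is that some propensity scores may not find a match.

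The same paragraph spreads the intervention group over sites: "we aim to recruit between 20 and 40 participants from each location for a maximum of 10 pilot locations". Study design and setting says of these sites that "they will differ in their local context, the way people are directed towards the eHealth tool, the specific support and guidance of participants", and that aftercare differs too. The description of step 2 of the approach leaves the choice between the two eHealth tools to local stakeholders. Under the recruitment procedure, controls come from neighborhoods of similar socioeconomic score where the approach is not offered.

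The analysis is named in one sentence: "We will use multiple regression models for the quantitative data using the matched data". Weighting or regression adjustment on the propensity score is the fallback. Neither the power statement nor the analysis text mentions an ICC, a design effect or location. Location is used only when the qualitative findings are compared within and across sites.

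**The concern.** Whether a person is exposed depends on where that person lives or receives care. No location holds both groups, so the treatment contrast lies between locations. People at one location share professionals, a tool, a way of being invited and a set of local services, and the study's premise is that such context shapes the response. Some correlation within locations is therefore to be expected. Matching on individual propensity scores balances measured covariates; it does not remove that correlation.

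Two things are at stake. The stated power is a figure in the protocol, and it comes from a formula that does not fit the design described beside it. And if the outcome regression ignores location, ordinary variation between places could be reported as an effect of the intervention.

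**Working it through.** **Inputs from the protocol.** SD 1.79, difference 0.55, two-sided 5%, 80% power, 175 analysed in the intervention group, and 20 to 40 recruited per location in at most 10 locations. I take 175 controls as well, since the recruitment target is equal in the two groups.

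**Assumed, because the protocol does not give it.** ICC of 0.01, 0.02 and 0.05. Control-group clustering is either absent or equal to that in the intervention group, because the number of control neighborhoods is not stated.

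**1. Reproduce the stated figure under independence.**
- SE = 1.79 × √(2/175) = 0.191.
- Power = Φ(0.55/0.191 − 1.96) = Φ(2.874 − 1.96) = 82%.
- Detectable difference = (1.96 + 0.8416) × 0.191 = 0.536, consistent with about 0.55.

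The stated power is thus an independent two-sample calculation with no allowance for clustering.

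**2. Slack.** The number needed per group for 0.55 is 2 × (1.79 × 2.8016/0.55)² = 166.3. The ratio 175/166.3 gives a tolerable design effect of 1.05. With 175 analysed in 10 locations, m = 17.5 per location. The slack is then used up at an ICC of 0.0525/16.5 = 0.003 if both groups are clustered, or twice that, about 0.006, if only the intervention group is.

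**3. Power with clustering (normal approximation).** DE = 1 + (m − 1) × ICC. With both groups clustered, SE = 1.79 × √(2·DE/175). With the intervention group only, SE = 1.79 × √((DE + 1)/175). Five locations of 40 recruited also fit the protocol's limits; that gives m = 175/5 = 35 analysed.

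| Locations | ICC | DE | Power, intervention group clustered | Power, both clustered |
|---|---|---|---|---|
| 10 (m = 17.5) | 0.01 | 1.165 | 79% | 76% |
| 10 (m = 17.5) | 0.02 | 1.33 | 76% | 70% |
| 10 (m = 17.5) | 0.05 | 1.825 | 68% | 57% |
| 5 (m = 35) | 0.01 | 1.34 | 76% | 70% |
| 5 (m = 35) | 0.02 | 1.68 | 70% | 60% |
| 5 (m = 35) | 0.05 | 2.70 | 56% | 42% |

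**4. Detectable difference at ICC 0.02, m = 17.5.**
- Intervention group only: 2.8016 × 1.79 × √(2.33/175) = 0.58.
- Both groups: 2.8016 × 1.79 × √(2 × 1.33/175) = 0.62.
- Both groups, with a t reference on 18 degrees of freedom (10 clusters per group, less 2): 0.65.

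**5. If the regression ignores location.** The unclustered standard error is too small by the factor √DE (both groups) or √((DE + 1)/2) (intervention group only). The true type I error of a nominal 5% test is 2 × (1 − Φ(1.96/factor)). At m = 17.5 and ICC 0.01 / 0.02 / 0.05 this is about 6% / 7% / 10% with the intervention group clustered and 7% / 9% / 15% with both.

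**The case against.** A reader might infer that the planned intervals are too narrow and that the planned test exceeds 5%. The article does not establish this. It names multiple regression but neither gives nor excludes a variance estimator or a random effect. Such detail is commonly left to an analysis plan, which is not shown here. So the interval and type I error figures hold only if the model is fitted as named, without accounting for location.

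A reader might also take the larger losses, with both groups clustered, as established. They are not. The cap of 10 locations and the 20 to 40 per location apply to the pilot locations only, and nothing says how many neighborhoods supply controls. If controls are spread thinly, the figures for intervention-group clustering are the relevant ones, and at ICC 0.01 with 10 locations the loss against the stated 80% is about one point.

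Nor do the documents show that the trial will fall short of 80%. Baseline scores are collected in both groups, and adjusting for them could recover power. At m = 17.5 with both groups clustered, and taking adjustment to scale the whole variance by (1 − r²), a baseline correlation of about 0.31 (ICC 0.01) or 0.46 (ICC 0.02) would hold 80%. But the power statement takes no credit for such adjustment, and adjustment alone would not correct a standard error that ignores location.

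What the objection leaves untouched is the power statement itself. The margin from 175 to 200 is assigned to unmatched propensity scores, so it is not a disguised design effect, and a later analysis plan cannot make the stated derivation fit the design.

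**Conclusion.** The 80% power statement is wrong as written, because it omits an allowance that the protocol's own design needs. The direction follows from the documents, given any within-location correlation beyond a very small one (about 0.003 to 0.006 with 10 locations). The size rests on the assumed ICC, on the number of locations and on whether controls are clustered. Over ICC 0.01 to 0.05, power runs from 79% to 57% with 10 locations, and from 70% to 42% with five locations and both groups clustered. These are normal approximations; a small-sample reference lowers them further. The risk to intervals and type I error is real but conditional on a regression that ignores location.

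**What to change.** State in the analysis section that the outcome model carries a random intercept for location (intervention) or neighborhood (control), or that standard errors are cluster-robust at that level. Either way, name a small-sample correction, such as Kenward-Roger or Satterthwaite for the mixed model or CR2 for robust errors, because clusters are few. Do not add location fixed effects or a random intervention slope. Location is nested in group, so fixed effects would absorb the intervention contrast, and a slope could not be separated from a group-specific random intercept.

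Restate the power or detectable difference with a design effect over a stated ICC range, with and without control-group clustering, using the number analysed per location. At ICC 0.02 with 10 locations, for example, the detectable difference is about 0.58 (intervention group clustered) to 0.62 (both), or about 0.65 with both clustered and 18 degrees of freedom. If baseline adjustment is to be counted on, state the assumed correlation.

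The cost is wording, a record of each participant's location or neighborhood in the analysis data, a less favourable stated figure and wider intervals. No extra recruitment is required.

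### The primary outcome is six domain scores at two follow-ups with no primary domain or time point named, while the sample size rests on an unadjusted 5% for one unnamed domain

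*Protocol article*

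**What the plan says.** Under Quantitative data collection, the protocol article names the 17-item Positive Health scale as the primary outcome. The scale "uses a six factor structure, comprising the factors physical fitness, mental functions, future perspectives, contentment, social relations, and daily life-management". The only scoring rule given is an average per factor on a 1-10 range; no total score is described.

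Under Data collection process, the quantitative data come from "surveys for the participants at 0, 3 and 12 months after participants joined the PIE-approach". Table 3 gives the same three time points for the control group. Study design and setting gives a follow-up period of 12 months, but no section says whether 3 or 12 months is primary.

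Under Quantitative analysis, primary and secondary outcomes are to be compared between participants and non-participants in the matched sample. No lead domain, lead time point, order of testing or global test is named. The sample size assumes 80% power, a two-sided 5% level and "a (norm-based) standard deviation of 1.79". It concludes that "we would be able to detect a difference of approximately 0.55 point in the score of one of the six domains" "with 175 participants with completed questionnaires and participating in the PIE approach" (the sentence names the scale between these two parts). To allow for mismatched propensity scores, "we aim for a sample of 200 respondents in both groups".

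**The concern.** A 5% level and 80% power describe one test. The primary outcome as defined gives six group comparisons at each of two follow-ups, so up to 12. The sample-size sentence covers one of these and does not say which.

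Two things are at stake. First, with nothing ranked in advance, a favourable result in any one domain at either follow-up could be presented as an effect on the primary outcome, and the chance of that happening with no true effect is well above 5%. Second, if a multiplicity adjustment is applied later, the stated detectable difference and power no longer hold at the planned size. Either way, the published pair of 5% and 80% is right only if one domain at one time point was chosen beforehand, and the article does not choose one.

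**Working it through.** **Inputs.** From Quantitative analysis: SD 1.79, difference 0.55, two-sided alpha 0.05, power 80%, 175 analysed in the intervention group, recruitment target 200 per group. From Quantitative data collection: six domain scores. From Data collection process and Table 3: two follow-ups. The documents give no correlations between domains or between time points, so these are assumed and varied below.

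**1. Reproducing the article's figure** (two independent means, equal groups).
- Standard error with 175 per group: 1.79 × √(2/175) = 0.191.
- Detectable difference at 80% power: (1.960 + 0.842) × 0.191 = 0.536.
- Power for 0.55: Φ(0.55/0.191 − 1.960) = 82%.
- Number needed for 0.55 at 80% power: 167 per group.

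The stated figure of about 0.55 therefore holds, slightly conservatively, with 175 read as per group. Reading 175 as the total would give 0.758, which does not match.

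**2. Chance of at least one false positive if every comparison is judged at 5% and there is no true effect.**

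For k independent tests this is 1 − 0.95^k:
- k = 6: 1 − 0.95^6 = 26.5%
- k = 12: 1 − 0.95^12 = 46.0%

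Positive correlation lowers these. By simulation (600,000 multivariate-normal draws, common correlation between domains):

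| Comparisons | Assumed correlation | Chance of at least one false positive |
|---|---|---|
| 6 (one time point) | 0 | 26.5% |
| 6 | domains 0.5 | 20.8% |
| 6 | domains 0.7 | 16.4% |
| 12 (both time points) | 0 | 46.0% |
| 12 | domains 0.5, time points 0.6 | 33.8% |
| 12 | domains 0.7, time points 0.7 | 25.9% |

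In the correlated 12-comparison rows, the correlation between two different domains at different times is the product of the two values. Higher correlations lower the figures further: six domains at 0.8 give 13.8%, and 12 comparisons at 0.9 (domains) and 0.8 (time points) give 16.3%.

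**3. What adjusting over six domains does to the stated power.** Bonferroni, which is also Holm's first step, uses alpha = 0.05/6 = 0.00833, with critical value 2.638.

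| Per group | Standard error | Detectable difference, (2.638 + 0.842) × SE | Power for 0.55, Φ(0.55/SE − 2.638) |
|---|---|---|---|
| 175 | 0.191 | 0.67 | 59% |
| 200 | 0.179 | 0.62 | 67% |

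Keeping 80% power for 0.55 at that level would need 257 per group. Adjusting over all 12 comparisons (alpha 0.00417) would leave 50% power at 175 per group and 58% at 200.

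**The case against.** The strongest reply is that the article never says each comparison will be tested at 5%. The 5% is a design input to the sample size. The analysis text speaks of estimating effects with regression models and sets no rule for declaring success. A multiplicity rule is commonly left to an analysis plan, and this is a condensed article. That stands: the absence of such a rule is not the finding, and a reader who infers that 12 tests at 5% will be run goes beyond the text. What remains is in the article itself: the definition of the primary outcome and the basis of the sample size do not match.

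A reader might also infer that 0.55 is wrong. It is not. It reads naturally as a per-domain figure that applies to any domain with SD 1.79, and it reproduces.

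A reader might merge the false-positive figures into a single range of 16-46%. That would mix six comparisons at high correlation with 12 independent ones. Domains of one questionnaire, measured twice on the same people, are unlikely to be independent, so the upper ends are limits and not expected values.

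Finally, this is a non-randomised realist evaluation with a largely explanatory aim, so strict family-wise control is more debatable than in a confirmatory trial. That lowers the severity. It does not remove the point, because Objective I is to measure impact, and the article declares a controlled design with a formal power calculation for effectiveness.

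**Conclusion.** The point holds as a mismatch between the primary outcome and the sample-size basis. The 5% level and 80% power are correct for one domain at one time point, but the primary outcome covers up to 12 comparisons and none is singled out.

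If each were judged at the only level stated, the chance of at least one false positive would be about 16-26% for six domains at one time point and about 26-46% for all 12. These ranges rest on assumed correlations from about 0.7 down to 0. They are conditional on that decision rule, which the article does not state. If the six domains are instead adjusted, power for 0.55 is about 59% at 175 per group, or 67% at 200, at Bonferroni's level or Holm's first step. Under Holm, later steps use less strict levels once earlier domains are rejected.

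This should be fixed and is a cheap improvement. The text does not support treating it as an error that invalidates the design.

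**What to change.** Before outcome analysis:

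1. Name one primary time point. Twelve months is a natural choice because it is the stated follow-up period; 3 months then becomes secondary.
2. Either test the six domains at that time point with Holm at an overall two-sided 5%, or name one domain in advance as primary and make the other five secondary.
3. If Holm is used, restate the detectable difference at its first step as about 0.67 with 175 per group (0.62 with 200), and power for 0.55 as about 59% (67% with 200). If one domain is pre-named, the present 0.55 can stand, with the domain stated.

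An average of the six domains as a single primary score is not proposed, because the article describes only factor-level scoring and gives no basis for a total.

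The cost is a change of wording and, under Holm, a less favourable stated detectable difference. No new data or enrolment is needed if that difference is accepted; keeping 80% power for 0.55 in each domain at Holm's first step would need 257 per group.
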